### Procedures

2.4

#### Beverage preparation

2.4.1

Beverage A (placebo) is going to be prepared using a noncaloric berry-flavored sweetener consisting of sucralose.

Beverage B (menthol solution) is going to be formulated by crushing and dissolving noncalorific menthol lozenge in warm deionized water, to obtain a solution with a concentration of 0.01%.

Prior to use, both solutions are going to be aliquoted for mouth rinse and warmed at room temperature. They will be served to each participant in individual bottles (75 ml at pre-cooling and 75 ml at per-cooling) and participants will be told to mouth rinse the beverage for 10 s and then to spit-out.

#### Introductory meeting

2.4.2

A previous presentation is going to be carried out by the research team to explain the study in detail to the participants. All stages of the study will be described, as well as the scales and procedures that are going to be adopted. Participants will be informed that they will have to swallow a telemetric pill 60 min before each trial, and to avoid consumption of alcohol and caffeinated products for 24 h before each trial, as well as strenuous exercise 48 h before testing. The participants will also be asked to drink 2–3 L of water in the day before each session. After understanding and agreeing with the information provided, the participants will sign the informed consent.

#### Familiarization session

2.4.3

All participants will undergo a familiarization session. All experimental procedures will again be fully described and tested in the field, so that the familiarization trial is as close as possible to the experimental trials resembles. The procedures and timings will be explained to participants.

#### Exercise protocol

2.4.4

The SAFT90 protocol emulates the intermittent and multi-directional nature of football match-play, with frequent changes in direction and activity [32]. It is based on time-motion analysis data from the English Championship level match play acquired during the 2007 season [31], and simulates the activity demands and physiological responses of football match play [33]. Players navigate around a 20 m agility course in an intermittent fashion via standing (0 km h^−1^), walking (5.5 km h^−1^), jogging (10.7 km h^−1^), striding (15.0 km h^−1^) or sprinting (maximal effort). The players cover 11.1 km in total, 18.5% of this distance (2.04 km) is performed at high-speed (≥15 km h^−1^) with 1269 changes in speed (every 4.3 s), and 888 changes in direction (180°) and 444 cutting manoeuvres over the 90 min (1332 directional changes). The protocol is divided into equivalent 15-min activity profiles, lasts 90 min and is performed on an indoor running surface. The type of movement activity and intensity is controlled using verbal signals from an audio MP3 file [31].

The participants of the present study will perform a standardized pre-match routine in terms of rest, nutrition, hydration and physical preparation and a 15-min warm-up will precede the 90-min simulation, which is going to be interceded by a 15-min passive half-time interval.

#### Environmental conditions measurement

2.4.5

The trial will be performed in an indoor facility, under high environmental stress conditions asper FIFA's guidelines: a Wet Bulb Globe Temperature (WBGT) between 29.4 and 32.1 °C [34]. Temperature, Relative Humidity and WBGT are going to be measured recurring to Kestrel 5400 Heat Stress Tracker (Kestrel Instruments®, Boothwyn, Pennsylvania, USA). In order to understand a possible heat acclimatization interference in the trial results, Temperature, Relative Humidity and WBGT are going to be recorded in the two days prior to the tests.

#### Outcomes

2.4.6

The primary outcomes of interest for this study involve physiological, physical and perceptual parameters. Physiological primary outcomes include heart rate (HR), SR and Tcore.

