### Sample size and recruitment

2.1

For sample size and statistical power calculations, power analysis was based on changes in TS after the internal administration via mouth-rinsing or ingestion of menthol solution. Considering a type I error of 5% and a power of 90%, with a statistical significance (p-value ≤0.05) and a moderate effect size of 0.54 (differences in TS were considered following Jeffries and Waldron results [30]), a total of 10 participants will be needed (using G*Power 3.1.9.2 ®). Considering a drop-out rate of 30% throughout the study, 13 participants as a buffer against attrition.

The Portuguese Football Federation (PFF) will contribute by recruiting referees through direct contact, databases, and referral sources. Following an initial telephone screen to determine the eligibility of potential participants, an orientation session (introductory meeting) will be scheduled to offer detailed information about the study, including the number and type of assessments, the length and nature of the exercise training, and the time commitment required to complete the study. After eligibility criteria confirmation, all participants will sign an informed consent form before being allocated to the study. Participants’ privacy and confidentiality will be guaranteed during and after investigation according to the Portuguese data protection law. Privacy, anonymity, and confidentiality of data/information identifying the participants will be strictly maintained. All information and results of the tests performed on the participants will be confidential. No one other than the investigators of this research will have access to the data.

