##### Physical performance

2.4.6.4

Physical performance responses will be measured using 100 Hz accelerometery, with Sonda 4.0 software (StatSports®, London, UK) to estimate total distance, sprint distance, accelerations, and decelerations.

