##### Perceptual parameters

2.4.6.5

Perceptual responses that are going to be evaluated in this study include 4 subjective scales: RPE, TC, perceived thirst (PT) and TS. RPE will be recorded through CR-10 Borg scale [39] that goes from 0 (“rest”) to 10 (“maximal effort”). TC is going to be assessed according to a 6-point scale from to −3 (“very uncomfortable) to 3 (“very comfortable”) [40]. PT will be evaluated recurring to a 7-point scale from 1 (“not thirsty at all”) to 7 (“very, very thirsty”) [27]. TS will be recorded with a 9-point scale (33) from −4 (“very cold”) to 4 (“very warm”) [41].

Secondary outcomes of this study include hydration status, *ad libitum* fluid intake during “water breaks”, lactate, and glucose blood levels.

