### Statistics

2.7

Statistical analysis will be performed using IBM SPSS statistics version 27.0, 2020 (SPSS Inc., an IBM Company, Chicago, IL, USA). To test the normality of distribution of the variables, the Shapiro-Wilk test will be performed. Baseline demographic and clinical characteristics of the participants will be analysed using descriptive statistics (mean, standard deviation, and range). For the continuous normal distributed variables, the one-way repeated measures analysis of variance (ANOVA) will be used to assess the association between the intervention and the perceptual, physical and physiological responses (thermal sensation, thermal comfort, perceived thirst, HR, accelerometery data, Tcore, SR, *ad* libitum fluid intake, lactate and glucose blood levels). Single time-point data will be examined for within-group effects across conditions using a one-way ANOVA. A two-way analysis repeated measures ANOVA will be used to test for within-group effects across time in both conditions. Missing data will not be included in the statistical analysis. Participants who discontinue or deviate from intervention protocols, and who meet exclusion criteria at some point of the intervention period, will be excluded. A *p* value of 0.05 will be considered statistically significant. Data will be reported according to the guidelines of consolidated standards of reporting trials (CONSORT) [28].

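### Eleven outcomes share primary status at an unadjusted 0.05 while the trial is sized on thermal sensation alone, so the 5% error rate does not hold for the primary conclusion

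*Protocol article*

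**What the plan says.** Section 2.4.6 (Outcomes) of the protocol article opens with "The primary outcomes of interest for this study involve physiological, physical and perceptual parameters". The variables are then named in three places:

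- Section 2.4.6: "Physiological primary outcomes include heart rate (HR), SR and Tcore".
- Section 2.4.6.4: accelerometry is used "to estimate total distance, sprint distance, accelerations, and decelerations".
- Section 2.4.6.5: the perceptual responses "include 4 subjective scales: RPE, TC, perceived thirst (PT) and TS".

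Only after that does section 2.4.6.5 turn to the next tier: "Secondary outcomes of this study include hydration status", followed by fluid intake, lactate and glucose.

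On testing, section 2.7 says that a *p* "value of 0.05 will be considered statistically significant". It assigns repeated measures ANOVA to all three domains, a one-way ANOVA to single time-point data and a two-way repeated measures ANOVA to data over time. It ranks no outcome above another and states no adjustment. On sizing, section 2.1 says that "power analysis was based on changes in TS"; no other outcome enters the calculation.

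**The concern.** The sample size treats one outcome as decisive, while the outcomes section gives ten others the same rank. With a flat 0.05 on each, the 5% error rate applies to each test and not to the trial's primary conclusion. The trial is not presented as exploratory: the abstract expects it to determine whether menthol rinsing changes perception, eases physiological strain and limits performance loss. A chance result on any one of the eleven could be reported as a primary finding, and the protocol gives a reader no way to tell it from the outcome the trial was designed to test.

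The choice of summary within TS is also open. Table 1 schedules TS 14 times per session. Six of those ratings (T9, T11, T13, T25, T27, T29) follow a rinse in the cooling stage, which T8 places at 18–20 °C and at rest, and which T24 repeats under the same conditions. An effect there is a different claim from an effect during exercise in the heat, which is the stated aim.

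**Working it through.** **The plan's own figure.** The article gives no family-wise error rate. Its only related figure is the 10 participants in section 2.1 (effect size 0.54, type I error 5%, power 90%). This does not follow from the stated inputs alone, because the metric of 0.54 is not given:

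- As a paired standardised difference (noncentrality 0.54·√n), 90% power needs 39 participants two-sided or 31 one-sided.
- As Cohen's f with two measures and correlation 0.5 (both assumed; λ = N·2·0.54²/(1 − 0.5)), it needs 12.

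That is a separate matter and does not enter the error rates below.

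**Number of primary outcomes.**

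| Domain | Section | Variables | Count |
|---|---|---|---|
| Physiological | 2.4.6 | HR, SR, Tcore | 3 |
| Physical | 2.4.6.4 | total distance, sprint distance, accelerations, decelerations | 4 |
| Perceptual | 2.4.6.5 | RPE, TC, PT, TS | 4 |
| **Total** | | | **11** |

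**Error rate, independent tests.** With one two-sided test at 0.05 per outcome and every null hypothesis true:

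- 11 tests: 1 − 0.95¹¹ = 1 − 0.569 = 0.431.
- 10 tests (RPE left out): 1 − 0.95¹⁰ = 1 − 0.599 = 0.401.
- Bound under any dependence, 11 tests: 11 × 0.05 = 0.55.

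**Error rate, correlated tests.** The article gives no correlations, so a common value ρ is assumed. Simulating 11 equally correlated normal test statistics (400,000 draws, two-sided critical value 1.96):

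| Assumed ρ | Chance of at least one p < 0.05 |
|---|---|
| 0 | 43% |
| 0.2 | 40% |
| 0.3 | 38% |
| 0.5 | 30% |
| 0.7 | 22% |
| 0.9 | 13% |

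For two-sided tests on jointly normal statistics, independence is the worst case (Šidák), so 43% is the upper figure for one test per outcome. It is not a ceiling for the whole plan. The two-way ANOVA yields a condition effect and a condition-by-time interaction for each repeatedly measured outcome, and the article does not say which one answers the primary question.

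**Error rate with one primary outcome.** One test at 0.05 gives 5%.

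**The case against.** **Multiplicity rules often sit in a statistical analysis plan, which is not shown.** That is fair, and a missing adjustment alone would not be a finding. The point rests on what the article does fix: eleven outcomes ranked primary, one used for sizing and a flat threshold. Choosing the primary outcome is a protocol decision.

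**RPE is absent from the bracketed list of analysed variables in section 2.7.** Correct. Section 2.4.6.5 still makes it primary, and as it is rated once (T39) the single time-point ANOVA would reach it. Without it, 43% becomes 40%.

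**Independence is implausible.** This stands. The thermal and thirst scales are rated together, the four physical variables come from one system, and section 2.4.4 controls activity and intensity by audio signal. The range of 22–30% at correlations of 0.7–0.5 is nearer to what one might expect, although those values are assumed.

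**Only results in favour of menthol would be claimed.** The independent figure is then 1 − 0.975¹¹ = 24%, and about 15% or 11% at correlations of 0.5 or 0.7. The matching nominal rate is 2.5%, so the inflation remains.

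**A reader might infer that the plan counts a p value of 0.05 on any outcome at any time point as success.** The article does not say so. Section 2.7 gives a threshold and no success rule, and single time-point data may simply mean variables measured once per session.

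**TS may be a poor sole primary.** It is subjective, and the Discussion concedes that participants will be very hard to blind to the beverage. That is a real cost of the repair, but it does not defend eleven equal primaries.

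**Conclusion.** The point holds. Eleven outcomes are primary, each faces an unadjusted 0.05, and the sample size covers one. The chance of at least one false primary claim is 43% under independence (40% without RPE) and about 22–30% at assumed common correlations of 0.7–0.5, against a nominal 5%. These figures assume one test per outcome and no true effect on any; more effects or time points per outcome would raise them.

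Two stronger conclusions are not supported. First, a reader might infer that false positives are likely. Even in the independent case the chance of one or more is below one half, and the chance of two or more is 1 − 0.569 − 11 × 0.05 × 0.599 = 10%. Nor does this arithmetic depend on the small number of completers. Second, a reader might infer that adjusting over all eleven would leave almost no power. That depends on the unstated metric of 0.54. At n = 10 and 0.05/11 = 0.0045, power is 7% if 0.54 is a paired difference, but a single unadjusted TS test then has only 33%. If 0.54 is Cohen's f with two measures and correlation 0.5, the figures are 43% and 86%. The case for one primary outcome rests on the mismatch with the sizing, not on a power figure.

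**What to change.** Before recruitment, amend sections 2.4.6 and 2.7:

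1. Name TS, the outcome used for sizing, as the single primary outcome, with one pre-specified summary tested once at two-sided 0.05.
2. Define that summary. One option that fits the aim of effects during exercise in the heat is the menthol–placebo difference in the mean of the six end-of-block ratings (T18, T20, T22, T31, T33, T35).
3. Confirm that 0.54 applies to the summary chosen. Section 2.1 speaks of changes after administration, which could mean the ratings straight after rinsing, so nothing shown ties 0.54 to the six-rating mean.
4. Relabel the other ten as secondary, reported with estimates and 95% confidence intervals and no confirmatory claim, or tested with a Holm adjustment. State in section 2.7 how RPE is analysed.
5. Bring the registered outcome labels into line.

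The cost is wording; every measurement stays in the schedule. The downside is that fewer outcomes can be called primary, the confirmatory claim becomes narrower than the three-domain aim, and it rests on a subjective rating open to unblinding. The report should state that limitation beside the primary result.

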##### Heart rate

2.4.6.1

HR will be measured through HR monitors (Polar H10 Heart Rate Sensor, USA). PolarH10 can accurately measure mean HR and low-frequency oscillations (up to 0.15 Hz) of HR at rest and during the protocol [35].

##### Sweating rate

2.4.6.2

SR is going to be calculated recurring to the following equation [36]:$$SR=\frac{Pre\;exercise\;body\;weight-postexercise\;body\;weight+fluid\;intake-urine\;volume}{exercise\;time\;in\;hours}$$

Pre-exercise body weight will be measured after participants voiding their bladder. Body weight will be measured on a digital platform scale (Seca, Hamburg, Germany), with minimal clothing, to the nearest 0.1 kg. Post-exercise body weight is going to be evaluated also with minimal clothing, after participants' towel-off themselves, at the half-time, before and after urine excretion (if needed), and at the end of the protocol. Fluid intake is going to be recorded via the measurement of mass change of the individual bottles, provided to the participants, at the warm-up and at the end of the first “water break” at the end of the session, to the nearest 0.1 ml (Seca, Hamburg, Germany). Urine volume will be determined through the difference of the referees' weight before and after urine excretion, using a digital platform scale. Participants will be advised not to rinse and spit out the fluids from the bottle at any time of the trial and that they should not drink any other beverages other than those provided by the researchers. Also, fluid intake will only be allowed in the 30th minute of each half, to simulate “cooling break” (“water break”) rule implemented by FIFA. FIFA's guidelines for extreme heat conditions (i.e. a WGBT of more than 32 °C) refer cooling breaks are mandatory in both halves of a match, around the 30th minute and 75th minute, so that football players and referees may rehydrate [37].

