#### Experimental trial protocol

2.4.7

The protocol of the trial will be divided into 39 phases (T1-T39) (Table 1 and Fig. 1). The participants will arrive at the testing facilities 1 h before the start of the warm-up. Schedule of the enrolment, interventions, and assessments is described in Fig. 2.

**Table 1 tbl1:** Description of the experimental trial phases.

**T1**	BodyCap® will be ingested by the participant.
**T2**	Then, participant's 24-h food recall diary will be collected.
**T3**	Hydration status will be assessed, after urine collection.
**T4**	After voiding their bladder, body mass will be measured on a digital platform scale, weighted with minimal clothing. Individual marked drink bottles will be distributed to the referee so that fluid consumed at “water breaks” may be recorded via the measurement of body mass changes. Participants will be informed that they may drink water *ad libitum*, on “water breaks”.
**T5**	Lactate and blood glucose levels are now going to be measured.
**T6**	Devices for assessing HR and physical performance parameters will now be placed on the referee and synchronized.
**T7**	TC, PT and TS are will be measured.
**T8**	Beverages (previously prepared and stored at the intended temperature) will be distributed to the referee. Total amount of beverages for pre-cooling previously described (75 ml of beverage A or B) will be divided into 3 equal parts and made available to the participant every 1 min. Beverages temperature will be monitored with a digital thermometer, to the nearest 0.1 °C (Proficook, Germany). The entire cooling stage will be carried out at a mild temperature of 18–20 °C, at rest. Participants will be instructed to swill both beverages for 10-s before spitting into a bowl without swallowing. The first 1/3 of the 75 ml of beverage will be administered.
**T9**	TC, PT and TS will be again evaluated.
**T10**	The second 1/3 of the 75 ml of pre-cooling beverage will be distributed.
**T11**	TC, PT and TS will be recorded.
**T12**	The third 1/3 of the 75 ml of pre-cooling beverage will be administered.
**T13**	TC, PT and TS will be again evaluated.
**T14**	Ambient temperature, relative humidity, and heat stress and WBGT will be recorded.
**T15**	Participants will start the 15-min warm-up.
**T16**	After the warm-up, TC, PT and TS will be again evaluated.
**T17**	The first 15-min block of the first half will start.
**T18**	TC, PT and TS will be recorded again after the end of the first block.

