**T19**	The second 15-min block of the first half will begin.
**T20**	TC, PT and TS will be evaluated after the end of the second block.
**T21**	First “water break” is now going to occur. The third 15-min block of the first half will start.
**T22**	TC, PT and TS will be assessed after the end of the third block and half-time period is going to start.
**T23**	If needed, participants will towel-dry themselves and then have their body mass measured (before and after urine excretion) with the same scale and while wearing the same clothes as the pre-exercise body mass assessment. Water bottles will be weighted.
**T24**	The same beverage (as in T8) will be provided to each participant, exactly in same conditions as in the pre-cooling phase. The first 1/3 of the 75 ml of the same beverage will be administered.
**T25**	TC, PT and TS will be recorded.
**T26**	The second 1/3 of the 75 ml of per-cooling beverage will be distributed.
**T27**	TC, PT and TS will be evaluated.
**T28**	The third 1/3 of the 75 ml of per-cooling beverage will be administered.
**T29**	TC, PT and TS will be accessed.
**T30**	The first 15-min block of the second half will start.
**T31**	TC, PT and TS will be recorded again after the end of the fourth block.
**T32**	The second 15-min block of the second half will begin.
**T33**	TC, PT and TS will be evaluated after the end of the fifth block.
**T34**	Second “water break” will occur. The third 15-min block of the second half will start.
**T35**	TC, PT and TS will be evaluated at the end of the sixth block.
**T36**	Lactate and blood glucose levels are going to be reassessed.
**T37**	Participants will towel-dry themselves and then have their body mass measured (before urine excretion) with the same scale and while wearing the same clothes as the pre-exercise body mass assessment. Water bottles will be weighed. Subsequently, the difference between the referee's weight at T4 and T37 is going to be calculated, to estimate whole-body sweat loss as well as SR during the protocol (the volume of fluid intake is going to be subtracted, as well as urine output).
**T38**	Hydration status is going to be evaluated, after urine collection.
**T39**	RPE will be assessed.

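### Sweating rate divides the mass lost from T4 to T37 by exercise time only, so its level in L/h does not match the interval weighed; the urine and fluid-intake terms also need tidying

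*Protocol article*

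**What the plan says.** Section 2.4.6 makes SR a primary outcome: "Physiological primary outcomes include heart rate (HR), SR and Tcore".

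Section 2.4.6.2 defines SR as pre-exercise weight minus post-exercise weight, plus fluid intake, minus urine volume. The denominator, with its equation markup, is "exercise\;time\;in\;hours". The article does not say whether this means 90 min or includes the warm-up.

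Table 1 sets the weighing window at T37: "the difference between the referee's weight at T4 and T37 is going to be calculated". On what lies inside it, section 2.4.4 says "a 15-min warm-up will precede the 90-min simulation, which is going to be interceded by a 15-min passive half-time interval". Section 2.4.7 adds "The participants will arrive at the testing facilities 1 h before the start of the warm-up", and T5 to T14 (blood sampling, device fitting, rinses, perceptual scales) fall between the T4 weighing and the warm-up.

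On the other terms:
- Body weight is taken "with minimal clothing, to the nearest 0.1 kg". Bottles are weighed to 0.1 ml.
- Urine: "Urine volume will be determined through the difference of the referees' weight before and after urine excretion, using a digital platform scale". This arises only at half-time, for those who need to void. T4 follows voiding and T37 precedes it, so the final void does not enter.
- Fluid intake at T4: "fluid consumed at “water breaks” may be recorded via the measurement of body mass changes". Section 2.4.6.2 instead uses the mass change of the bottles, and T23 and T37 weigh the bottles.
- The section 2.4.6.2 formula adds fluid intake; T37 says it is subtracted.

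**The concern.** A rate should divide a loss by the time over which the loss occurred. Here the loss covers at least 120 min plus a lead-in, and the divisor covers 90 or perhaps 105 min. The reported L/h is then neither the rate during exercise nor the rate over the interval weighed. The level of a primary outcome, and any menthol-placebo difference quoted in L/h, would be hard to interpret.

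Three smaller defects sit in the same definition:
- A half-time void puts four rounded body weights into SR instead of two.
- Body mass is taken only at T4, T23 and T37, never around a water break, so T4's method cannot yield intake. Ad libitum intake is also a secondary outcome measured by the same procedure.
- The sign of the intake term differs between the formula and T37.

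**Working it through.** The article gives no SR value, SR precision or SR-based power, so there is no figure of its own to reproduce.

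**1. Length of the window.** Warm-up 15 + exercise 90 + half-time 15 = 120 min (section 2.4.4). To this come the water breaks (1 min each in the Discussion) and the time from T4 to the start of warm-up. That lead-in is at most 60 min less T1 to T3.

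**2. Overstatement of the level.** Set the exercise sweat rate to 1. Let w and h be the relative rates in warm-up and half-time, and p the relative rate over a rest of m min before warm-up. All four are assumptions.

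Loss over the window = 90 + 15w + 15h + p·m. Loss over the time counted = 90, or 90 + 15w if exercise time includes the warm-up. Overstatement = (first / second) − 1.

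| w | h | p, m | Window loss | Divisor 90 min | Divisor 105 min |
|---|---|---|---|---|---|
| 0.25 | 0.25 | none | 97.5 | 97.5/90: 8% | 97.5/93.75: 4% |
| 0.5 | 0.5 | 0.05, 30 | 106.5 | 106.5/90: 18% | 106.5/97.5: 9% |
| 1 | 0.5 | 0.05, 30 | 114 | 114/90: 27% | 114/105: 9% |
| 1 | 1 | none | 120 | 120/90: 33% | 120/105: 14% |
| 1 | 1 | 0.10, 45 | 124.5 | 124.5/90: 38% | 124.5/105: 19% |

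For scale, the Introduction's 1.60 L match loss gives 1.60/1.5 = 1.07 L/h, 1.60/1.75 = 0.91 L/h and 1.60/2.0 = 0.80 L/h.

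**3. Effect on the comparison.** The paired t statistic is mean(d) / (SD(d)/√n). Dividing every d by one constant scales numerator and denominator alike, so t does not change. A check on 13 simulated differences, divided by 1.5 h and by 2.0 h, gave the same t. The ratio of the two condition means is also unchanged. The difference in L/h scales with the divisor.

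**4. Rounding.** One weight read to 0.1 kg has rounding SD 0.1/√12 = 0.0289 kg.
- Two weights: 0.0289 × √2 = 0.041 kg, or 0.041/1.5 = 0.027 L/h; worst case ±0.1 kg, or ±0.07 L/h.
- Four weights (void at half-time): 0.0289 × √4 = 0.058 kg, or 0.038 L/h; worst case ±0.2 kg, or ±0.13 L/h.

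Simulation gave the same SDs, 0.027 and 0.038 L/h. With an assumed within-person SD of 0.10 L/h, the total SD rises by √(0.10² + 0.0385²) / √(0.10² + 0.0272²) − 1 = 3.4%. With 0.30 L/h it rises by 0.4%.

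**5. Sign of intake.** The formula gives loss + intake − urine; T37 read literally gives loss − intake − urine. The two differ by twice the intake, divided by the time used.

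**The case against.** The strongest reply is that the trial asks for a menthol-placebo contrast in a crossover with the same timings in both sessions, and a common divisor cancels. This stands. A reader might infer that the comparison itself is biased; the documents do not support that. The cancellation covers the divisor only. The lead-in has no fixed length, so resting loss could differ between a participant's two sessions, though at the stated 18–20 °C this is probably small.

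A reader might also divide the roughly 122 min from warm-up to finish by 90 or 105 and report 36% or 16%. Those figures need full-rate sweating throughout half-time. Section 2.4.4 calls half-time passive, and T24 gives the rinse under the pre-cooling conditions, which T8 sets at 18–20 °C and at rest. If nobody sweated at half-time or before warm-up, and exercise time meant 105 min, the overstatement would vanish.

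The direction is not certain either. SR is too high if the section 2.4.6.2 formula is used. If T37's subtraction of intake is followed, SR falls by twice the intake over time, which could outweigh the divisor effect.

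Finally, a reader might call SR seriously noisy because of the urine method. The extra rounding affects only those who void at half-time, and the ±0.2 kg worst case needs four maximal errors acting together. The T4 wording is an editorial slip, since the same sentence hands out marked bottles, but as written its method cannot work.

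**Conclusion.** The mismatch is real and worth correcting because SR is a primary outcome. Under the section 2.4.6.2 formula, the absolute SR is too high by about 8% to 33% with a 90-min divisor (38% with the assumed lead-in). With a 105-min divisor it is about 4% to 14% (19% with the lead-in). The difference in L/h is inflated by the same factor if the two conditions differ proportionally over the whole window. These ranges rest on assumed relative sweat rates, since the article gives none, and on intake being added. The paired test and the relative difference are not biased by a constant divisor.

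The urine method is a minor, avoidable loss of precision: 0.038 against 0.027 L/h, for half-time voiders only. The T4 wording and the sign of intake at T37 are contradictions within the text, and the sign may matter more to the SR level than the divisor does.

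**What to change.** - **Interval.** Take the start weight just before warm-up and divide by the time between the two weighings used, fixed and identical in both sessions. Alternatively, state T4 to T37 as the interval and divide by its recorded elapsed time; this brings in low-sweat rest whose length may vary. Either way, say what the divisor is.
- **Half-time urine.** Collect it in a container and weigh it on the scale used for the bottles. Urine is already collected at T3 and T38.
- **T4.** Replace body mass changes with the mass change of the bottles.
- **T37.** Reconcile the intake term with the section 2.4.6.2 formula, so that one sign applies throughout.

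The cost is wording in section 2.4.6.2 and Table 1, plus one container weighing per participant who voids. The reported SR will be somewhat lower and will be an average that includes half-time. A start weight just before warm-up falls after device fitting at T6, so the devices must be handled the same way at both weighings.

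The T23 weight should not be used to report SR separately by half as part of this change. Two 0.1 kg readings over 0.75 h give a rounding SD of 0.041/0.75 = 0.054 L/h for every participant, more than the 0.038 L/h that the urine change removes for a few.
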